**Other Measures:**

Expectations: Subjects will be asked to rate their expectations for improvement at baseline. Subjects will be asked: “At the conclusion of this three week trial how much to you expect your IBS symptoms to improve?” Their responses will be recorded on a 10 point scale with the following anchors: “0=No Improvement” and “10=Complete Relief of IBS Symptoms.”

Patient-Practitioner Relationship rating: The Working Alliance Inventory (WAI) scale will be used to measure the patient’s perception of the relationship with the practitioner. The WAI was developed by Horvath and Greenberg (1989) to measure three components of the patient-practitioner relationship: goal, task and bond. Data shows that WAI is reliably correlated with a variety of counselor and client self-reported measures.

Short Qualitative Description Report: At the completion of the study, after all assessment have been made patients who took the placebo will be asked to briefly describe in their own words responses to the following questions:

1. What do you think about the idea of taking placebo?

2. Did you expect it to work or were you skeptical?

3. What did you think was in the placebo pills?

4. Is there anything you would like to comment on about concerning your experience in the trial?

Subjects on the waitlist will be asked:

1. Were you disappointed to be in the waitlist?

2. What did the like the most and least about the trial?

3. is there anything else you would like to comment on about concerning your experience in the trial?

**Planned Statistical Analyses**

For continuous measures (i.e., IBS-SSS and IBS-QoL), we will conduct analyses of covariance (ANCOVA) controlling for baseline scores to test whether the open-label placebo yields a significantly greater benefit at the three-week endpoint than any improvement occurring in the wait-list control. For categorical measures (i.e., IBS-GIS, IBS-AR), we will conduct chi square tests to determine whether the proportion of responders in the open-label placebo condition significantly exceeds the proportion of responders in the wait-list control. All tests will be two-tailed with alpha set at .05.

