**D. Data Analysis and Power Analysis:**

Outcome Measures: The following outcome measures will be used in this study. All questions will be asked at baseline, midpoint and endpoint with the exception of IBS-Global Improvement Scale (IBS-GIS) and IBS-Adequate Relief (IBS-AR).

IBS Global Improvement Scale (IBS-GIS): “Compared to the way you felt before you entered the study, have your IBS symptoms over the past 7 days been: 1) “Substantially Worse”, 2)”Moderately Worse, 3)”Slightly Worse”, 4)”No Change”, 5) ”Slightly Improved”, 6)”Moderately Improved” or 7) “Substantially Improved” (Kellow, 2003, Lembo, 2001; Gordon, 2003). A responder was defined as a patient who answered that their symptoms were either “moderately improved” or “substantially improved”. This will be our primary outcome.

IBS Global Symptom Assessment (IBS-GSA): Overall IBS symptoms will be rated by the subject by answering the following global question at the end of each week: Before you started taking the study “medication,” you said that you had [answer (in words) to baseline question 1 will be inserted here]. Compared to how you felt then, how would you rate your overall IBS symptoms during the past week? Possible answers are one of the following: Significantly relieved (+3);

Moderately relieved (+2); A little bit relieved (+1); Unchanged (0); A little bit worse (-1); Moderately worse (-2); Significantly worse (-3).

IBS Adequate Relief: Have you had adequate relief of your IBS symptoms over the past week? Yes or no

IBS Symptom Severity Scale (IBSSSS): The IBS Symptom Severity Scale (IBS-SSS) contains five questions that measure on a 100-point VAS, the severity of abdominal pain, the frequency of abdominal pain, the severity of abdominal distention, dissatisfaction with bowel habits, and interference with quality of life (Francis, 1997). All five components contribute to the score equally yielding a theoretical range of 0-500, with a higher score indicating worse condition. Previous studies have established that scores below 175 represent mild IBS symptoms, 175–300 represents moderate severity, and scores above 300 represent severe IBS (Francis, 1997). The total severity score on the IBS-SSS was treated as the gold standard measure of IBS severity. In the study by Francis et al., a decrease of 50 points correlatedwith improvement in clinical symptoms and was therefore considered to be a responder.

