**Statistical Power**

Our previous trial of placebo effects in IBS produced effect sizes that ranged from d=.5 to d=.9. Using two-tailed t-tests with alpha set at .05, a total sample size of 80 will have 60% power to detect the lower end of this range and 94% power to detect the upper end of the range. Using the same assumptions but a total sample size of only 50, we would have power between 41% and 88%.

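### The week-3 ANCOVA for IBS-SSS and IBS-QoL makes no use of the midpoint scores, which leaves these two secondary contrasts open to bias if loss to follow-up depends on the midpoint score and differs between arms

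*Protocol*

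**What the plan says.** In the Protocol, Overall Design sets three assessments: baseline, midpoint and three weeks. Outcome Measures (under Data Analysis and Power Analysis) says "All questions will be asked at baseline, midpoint and endpoint with the exception of" two instruments, IBS-GIS and IBS-AR. IBS-SSS and IBS-QoL are not among the exceptions, so both have a scheduled midpoint score.

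Planned Statistical Analyses fixes the method for these two scales as ANCOVA, "controlling for baseline scores to test whether the open-label placebo yields a significantly greater benefit at the three-week endpoint". Mediation Analyses uses the same model with the mediators added. Neither section brings in the midpoint score of the outcome.

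The primary outcome is the IBS-GIS responder rate, compared by chi-square. IBS-SSS and IBS-QoL are therefore secondary.

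The protocol states no rule for a missing week-3 score and no expected loss. Statistical Power works from a t-test and says that "a total sample size of 80 will have 60% power to detect the lower end of this range". Eighty is also the number to be randomised under Overall Design.

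**The concern.** A model of the week-3 score needs a week-3 score. With nothing further specified, a patient who attends the midpoint and then leaves drops out of the comparison, although a post-baseline score is in hand.

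The arms are unblinded from the first practitioner contact. Controls know that they are on a no-treatment waitlist. Placebo patients are told that benefit depends on taking the pills carefully. Arm-specific reasons to leave are plausible. If they are also linked to how the patient felt at the midpoint, the patients left at week 3 are selected differently in the two arms, and adjustment for baseline alone does not remove that. The error can go either way: losing worse controls understates the benefit, and losing worse placebo patients overstates it. The trial is meant to supply preliminary data for a larger grant, so the estimated effect matters as well as the test.

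**Working it through.** **1. The plan's own power figure.** Inputs from Statistical Power: "Using two-tailed t-tests with alpha set at .05", d = 0.5, total 80 (40 per arm). Two-sample t-test: noncentrality d × √(n/2) = 0.5 × √20 = 2.236 on 78 degrees of freedom, giving 59.8%. The stated 60% reproduces. (At d = 0.9 the same inputs give 97.8%, not the stated 94%. That is a separate matter and nothing here depends on it.)

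**2. Loss and power.** The protocol gives no loss rate, so 10% and 20% are assumed. ANCOVA power uses the effective size d/√(1 − r²), where r is the baseline to week-3 correlation (assumed): 0.5/√0.91 = 0.524 for r = 0.3, and 0.5/√0.75 = 0.577 for r = 0.5.

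| Evaluable | t-test | ANCOVA, r = 0.3 | ANCOVA, r = 0.5 |
|---|---|---|---|
| 80 | 59.8% | 63.9% | 72.2% |
| 72 | 55.3% | 59.2% | 67.6% |
| 64 | 50.4% | 54.1% | 62.3% |

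**3. Where bias comes from.** Regress the week-3 score on baseline, arm and midpoint score among completers, and call the midpoint slope β. Completers' ANCOVA then differs from the estimate that uses every midpoint score by

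β × (arm difference at midpoint among completers − arm difference at midpoint among all patients).

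With correlations of 0.5 (baseline–midpoint), 0.5 (baseline–week 3) and 0.7 (midpoint–week 3), β = (0.7 − 0.5 × 0.5)/(1 − 0.5²) = 0.45/0.75 = 0.60. A shift of 0.15 SD in the midpoint difference, caused by selective loss, therefore moves the week-3 contrast by 0.60 × 0.15 = 0.09 SD. If loss does not shift the midpoint difference, there is no bias.

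**4. Simulation, assumed inputs.** 40 per arm, true week-3 effect 0.50 SD, midpoint effect 0.35 SD, the correlations above, 4,000 trials per case. The percentage is the dropout probability at an average midpoint score. Entries are the mean estimated benefit in SD.

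| Loss after midpoint | ANCOVA, 10% | ANCOVA, 20% | Midpoint used, 20% |
|---|---|---|---|
| Random | 0.50 | 0.50 | 0.50 |
| Worse score raises loss, same in both arms | 0.49 | 0.48 | 0.50 |
| Worse score raises loss in placebo arm only | 0.56 | 0.59 | 0.50 |
| Opposite directions in the two arms | 0.61 | 0.69 | 0.50 |

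Under 20% random loss the standard error is 0.219 for completers' ANCOVA, 0.211 with the midpoint used and 0.196 with no loss. Power is about 62% against about 65%.

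**5. Milder settings.** With 3% to 18% loss per arm, completers' ANCOVA gave 0.49 when the mechanism was equal in both arms, and 0.44 to 0.45 or 0.54 when midpoint-dependent loss differed by arm. The midpoint model stayed at 0.50. Its power gain was about 2 to 4 points under balanced loss and 10 to 12 points when more controls were lost.

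A further set (correlations 0.6, 0.5 and 0.7, midpoint effect 0.4 SD, 2,000 trials per case) compared completers' ANCOVA with the midpoint model, loss given as control against placebo:
- 19% against 4% lost: 0.46 SD and 58% power, against 0.51 SD and 69%.
- 19% against 15% lost: 61% against 65% power.
- 11% against 8% lost: 69% against 70% power.

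Under no true effect, with 19% against 6% lost, ANCOVA was off by 0.05 SD and the midpoint model by 0.00.

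**The case against.** A week-3 ANCOVA adjusted for baseline is a valid analysis and answers the three-week hypothesis directly. With complete data the alternative gives the same answer. The outcomes are secondary, follow-up is only three weeks, and both arms get the same practitioner time. All of this stands, and it limits the weight of the point.

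A reader might infer more than the documents support:

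- *That midpoint-only patients are discarded by rule.* No such rule is stated. ANCOVA is compatible with imputation that uses the midpoint score, and missing-data handling is commonly left to a SAP, which is not at hand. The point holds only for the model as stated, with no further rule.
- *That the contrast is biased.* The documents show neither a loss rate nor a pattern of loss. Bias needs loss that is related to the midpoint score and differs by arm.
- *That the protocol itself signals unequal dropout.* The question "Were you disappointed to be in the waitlist" is put after all assessments, so it goes to patients who finished. It says nothing about who leaves.
- *That the stated 60% power is wrong.* It reproduces for 80 patients. It is an unadjusted t-test on effect sizes with no outcome named, and baseline adjustment can offset modest loss (62.3% at 64 evaluable if r = 0.5, though 54.1% if r = 0.3). The section also shows a much smaller sample: "a total sample size of only 50, we would have power between 41% and 88"%.
- *That the midpoint model cures dropout.* It performs perfectly above because loss was generated from the observed midpoint score, which is what the model assumes.

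**Conclusion.** The point stands in limited form. The protocol chose a model for IBS-SSS and IBS-QoL that leaves out a score it collects, and another standard model uses that score at no cost to the week-3 question.

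Under random or similar loss, the consequence is nil or negligible bias and a small loss of precision. Under midpoint-dependent loss that differs by arm, the bias is about 0.04 to 0.06 SD at 3% to 18% loss per arm. That is 0.04/0.50 = 8% to 0.06/0.50 = 12% of a true effect of 0.50 SD, and 0.05 SD is about a quarter of a standard error (0.05/0.21 = 0.24). In the two more extreme cases at 20% it is 0.09 and 0.19 SD. The direction cannot be known in advance.

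Loss rates, mechanisms and correlations are all assumed. The documents give no standard deviation, so the bias cannot be put into scale points. The IBS-GIS comparison is untouched, and no error in the stated 60% power is claimed.

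**What to change.** In Planned Statistical Analyses, replace the week-3 ANCOVA for IBS-SSS and IBS-QoL with a repeated-measures model on the midpoint and week-3 scores. Include arm by visit and baseline by visit, use an unstructured covariance, and include all randomised patients with any post-baseline score. Keep the arm difference at week 3 as the tested contrast.

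Optionally, note in Statistical Power that the 60% takes all 80 patients as evaluable, and give the t-test figures for 72 and 64 (55.3% and 50.4%).

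The cost is a change of wording and slightly more analysis work with standard software. No new data are needed, and with complete data the week-3 result matches ANCOVA. The limits should be stated: the model corrects only for loss explained by observed scores. It does not correct for loss driven by unobserved changes after the midpoint, and it recovers no post-baseline information from patients lost before the midpoint.

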**Mediation Analyses**

We also plan to conduct mediation analyses to determine whether any of the hypothesized mechanisms of the open-label placebo response (i.e., expectations, adherence, and the quality of the patient-practitioner relationship as measured by the WAI) can mediate the effects of experimental group assignment. For continuous variables (i.e., IBS-SSS and IBS-QoL), these analyses will take the form of analyses of covariance (ANCOVA), controlling for the influence of the mediators as well as the baseline symptom scores. For categorical outcome variables (i.e., IBS-AR, IBS-GSA, IBS-GIS) we will use logistic regression models. All analyses will be two tailed, with alpha set at .05. If the hypothesized mediators influence outcome, then the association between experimental group assignment (i.e., open-label placebo vs. wait list control) and outcome should significantly diminish or disappear altogether (in the case of complete mediation) once the mediators are added to the model.

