our published meta-analysis that showed on average 42% of patients on placebo treatment improve in IBS RCTs (Patel et al 2005). Furthermore, the patients will be informed about our recent IBS study showing that placebo acupuncture was as effective as current medications for IBS but without the side effects. Also during this discussion, to support expectation and to insure that patients are not conflicted about placebo improvement somehow being a sign that the IBS is “in their heads,” the physician or nurse practitioner will also explain that placebo effects change human physiology and can improve immune, endocrine, and pain mechanisms and that response to placebo is a demonstration of “self-healing capacities.” During the discussion the treating physician or nurse practitioner will naturally and clearly repeat the words that are stated in the informed consent that informs the patient that he/she will receive “an inert substance (the placebo), something like a sugar pill, that has been shown in rigorous clinical tests to somehow produce significant self-healing processes in IBS patients.”

The treatment will also seek to maximize the contributions of adherence

and conditioning to the placebo effect of IBS. Patients will be told that it is critical

to take the pill two times daily with meals and that scientific evidence suggests

that the positive effects of the pill taking will only happen if one is meticulous

about taking the pill. Patients will be asked to describe situations in their life

where taking pills had positive effects in their lives. When such a situation is

remembered, patients will be encouraged to remember this context when

they’re taking their inert medications. To again take any negative

connotation about “the symptoms are in their head” patients will be informed

about how conditioning with pills can “automatic trigger” a conditioning

response like Pavlov’s dog who salivate to a bell. The entire patient-

practitioner encounter will take place in the context of a positive, confident

and supportive relationship. As much as possible, we will follow the protocol

used in our last RCT and to ensure that the interaction includes each of

the following points: the conveyance of a warm and friendly manner,

definite communications of empathy, behaviors that demonstrate

active listening, and an empathic expression of confidence in the likelihood

of improvement when taking pills, even inactive pills. A warm manner will have

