the following characteristics: hand shaking, exchange on whether to use first or

last names, eye contact but not over gazing, courtesy, friendliness, orienting

the patient during examination, time for questioning, head nodding, forward

leaning, and uncrossed legs and arms. Empathy will be invoked with the

physician stating how he/she understands the difficulties that people with IBS

live with. Confidence will be fostered as the practitioner explains the

evidence concerning placebo effects. At the end of the first visit the patient will

be given enough placebo for the first half of the study and a mid-point follow-up

will be scheduled. The mid-point follow-up will be similar to the baseline

but abbreviated in time and will also include scheduling a final evaluation.

The entire discussion will take approximately 20 minutes.

Description of the no treatment usual care control arm:

The purpose of this arm is to match the ‘active” arm for time with practitioner. In

the informed consent, patients will be told that they will be randomized into

either the placebo or no treatment waitlist usual care arm. It will be explained,

if they are randomized to the latter, they will continue their regular IBS regimen

and will contribute to the observational IBS group. During the visits, t

he practitioners will seek clear descriptions of the patient’s symptoms

and life-style in relationship to their IBS. This evaluation will be in an identical context of the “active” arm with the exception that no attempt will be made to marshal positive expectation, conditioning response, or confidence of improvement or adherence to their IBS regimen. In order to fill the 20 minutes, the physician or nurse practitioner will provide educational support concerning IBS and go over the patient’s knowledge of IBS and how their life-style, including diet, exercise and stress contributes to their symptoms. We also review their current therapeutic regimen for IBS but we will not attempt to alter it during the study period.

Fidelity of treatment: To monitor fidelity to the time of treatments, the physician or nurse practitioner will put on a timer before the patient enters the room and turn off the timer after she/he leaves and record the time on the chart.

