#### I. Possible Risks

| Safety Measurements  The safety of subjects will be monitored at each study visit  - AEs  -Vital signs and body weight  - Physical exam  - Concomitant medication use  *Risks:*  *Subjects may experience normal fluctuations in their IBS symptoms (i.e., abdominal pain or discomfort). But since no active treatment is being given and patients are being evaluated 3 times over 3 weeks by a practitioner experienced in IBS there is minimal risk to the patient.* |
| --- |

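### Adherence is a planned mediator of the placebo versus wait-list effect, but the protocol describes no measure of it, and study-pill adherence has no meaningful value in the wait-list arm

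*Protocol*

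**What the plan says.** Protocol, Mediation Analyses, names three candidate mediators of group assignment: "expectations, adherence, and the quality of the patient-practitioner relationship as measured by the WAI". They are added to an ANCOVA with baseline score for IBS-SSS and IBS-QoL, and to logistic models for IBS-AR, IBS-GSA and IBS-GIS. If the mediators influence outcome, the association between arm and outcome "should significantly diminish or disappear altogether (in the case of complete mediation) once the mediators are added to the model".

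The places in the protocol that bear on adherence are these:

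- Section F, description of the placebo arm: patients are told that it is critical "to take the pill two times daily with meals", and that evidence suggests "that the positive effects of the pill taking will only happen if one is meticulous". At the first visit each patient will "be given enough placebo for the first half of the study and a mid-point follow-up" is arranged.
- Section F, description of the control arm: no study pills are given. Adherence appears only among the things that practitioners will not try to promote: "confidence of improvement or adherence to their IBS regimen".
- Section F, Fidelity of treatment: the check is a visit timer, "To monitor fidelity to the time of treatments".
- Other Measures: an expectation scale and the WAI are defined. Nothing is defined for adherence, and the exit questions do not ask about intake.
- Section I, Possible Risks: the safety items include "Concomitant medication use", which does not record study-pill intake.

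**The concern.** There are two linked problems. First, one of three named mediators has no described data source. Section B makes adherence one of four components of the intervention, so pill intake is also the basic description of exposure to the treatment under test. What is recorded at visits is a protocol matter: an analysis plan can define a variable from collected data but cannot supply data that were not collected.

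Second, the model does not suit the variable. A mediator of a between-arm effect needs a value with the same meaning in both arms, and adherence to study pills has none where no pills are given. At stake are the adherence part of the mediation analysis and the report's ability to say how much of the regimen was taken, in a trial meant to supply preliminary data for a larger grant.

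**Working it through.** The plan states no figure on this point, so there is none to reproduce. The check has two parts.

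**Is a measure described?** Section F, the outcome measures, Other Measures and Section I were read for a pill count, bottle return, diary or adherence question. None is described. The regimen is 2 doses a day for 21 days, or 2 × 21 = 42 planned doses for each of 40 placebo patients.

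**What would the between-arm model do with a pill count?**

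*Wait-list values missing, incomplete cases deleted.* All 40 wait-list patients leave the model. Arm is then constant and its effect cannot be estimated.

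*Wait-list values coded zero.* Let placebo-arm adherence have mean m and SD s, with 40 patients per arm. The documents give no adherence figures, so m and s are assumptions. The share of the count's variance explained by arm is

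R² = (m²/4) / (m²/4 + s²/2), with VIF = 1/(1 − R²) and SE ratio = √VIF.

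| m, s | R² | r with arm | VIF | SE ratio |
|---|---|---|---|---|
| .90, .10 | .2025/.2075 = .976 | .99 | 41.5 | 6.4 |
| .85, .15 | .1806/.1919 = .941 | .97 | 17.1 | 4.1 |
| .75, .25 | .1406/.1719 = .818 | .90 | 5.5 | 2.3 |

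In this coding the adjusted arm coefficient equals the placebo-arm regression line extrapolated back to zero pills, minus the wait-list mean. That is an extrapolation well outside the data when most patients take most pills, which is why it is imprecise.

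*Simulation.* The settings were a linear model without a baseline covariate, outcome SD 1, 40 v 40, beta-distributed counts with exactly the means and SDs above, no effect of the count on outcome, and two-sided .05. The effect d=.7 is assumed, as the middle of the .5 to .9 range in Statistical Power.

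- Without the count, the arm effect is significant in about 87% of runs.
- With the count added, 92%, 88% and 71% of those significant effects lose significance (rows in table order). Repeat runs differ by about a point, giving about 71% to 93%.
- Over d=.5 to .9 the loss runs from about 60% (m=.75, s=.25, d=.9) to about 93% (m=.90, s=.10, d=.5).
- The mean adjusted arm coefficient stays at about 0.70, and the test of the count's own effect rejects in about 5% of runs. The loss is one of precision, not bias.

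**What could a count support?** Within the placebo arm (n=40, two-sided .05, 80% power) the smallest detectable correlation is tanh((1.960 + 0.842)/√37) = 0.43. Such an analysis is exploratory only.

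**The case against.** **Not described is not the same as not collected.** A reader might infer that pills will go uncounted. The protocol does not say so. Naming adherence as an analysis variable suggests an intent to record it, dispensing in two halves offers a natural counting point, and the case report forms are not shown. This stands: the supportable statement is that no measure is described and the report may be unable to state exposure.

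**The model can be fitted.** With zeros for the wait list it runs, and the arm coefficient is about unbiased when the count has no effect. The protocol fixes neither coding, and an analysis plan might. This stands against any claim that the model is impossible. But neither coding gives a useful answer, so leaving the choice to an analysis plan does not repair it.

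**The protocol does not equate a lost p-value with mediation.** A reader might infer that the plan would manufacture mediation. It would not: its wording says what should follow if mediators matter, and the count's own test holds its 5% level. The loss of significance harms only if it is misread. The risk remains because the section names no test of the indirect effect and describes mediation through the weakening or disappearance of the arm association.

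**Adherence to the usual IBS regimen may have been meant.** That would exist in both arms, at least for patients on a regimen. No measure of it is described either, and the protocol does not name it as the mediator.

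**It is a secondary analysis.** True. The other two mediators have named measures.

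**Conclusion.** The point holds. Adherence is planned as a between-arm mediator without a described measure, and study-pill adherence cannot be meaningfully interpreted in that model. Deleting incomplete cases makes the arm effect inestimable. Zero coding inflates its standard error about 2.3 to 6.4 times and, at an assumed d=.7, removes significance from about 71% to 93% of significant arm effects.

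These sizes rest on assumed adherence (mean 75% to 90%, SD 25 to 10 points) and, for the percentages, on a linear model with no effect of the count. The logistic models were not simulated.

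A reader might go on to doubt the main result. Nothing supports that: the primary chi-square comparison of IBS-GIS responders does not use adherence. The amendment is worth making, but the trial's main conclusion does not depend on it.

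**What to change.** - **Mediation Analyses:** remove adherence from the between-arm models.
- **Other Measures:** add, for the placebo arm, that patients bring their bottles to the midpoint and endpoint visits and staff record pills dispensed minus pills returned.
- **Use of the count:** describe exposure (share of the 42 planned doses taken) and examine one exploratory association with outcome within the placebo arm. State that it is not causal, since Section B itself allows that adherence may be a marker of other health behaviours.

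The cost is one count at each of two visits already scheduled, a line on the case report form and a short amendment. The downsides are slight staff and patient effort, and counts can overstate intake if pills are discarded.
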